##### Virtual Badges

Research shows that learning tasks can be made more engaging and memorable when participants are given proximal goals and benchmarks to strive for and when their accomplishments are reinforced with rewards [95,96]. Participants assigned to this enhancement arm receive virtual flower badges for accomplishing tasks and meeting milestones. These colorful badges are collected on participants’ personal green garden plot, and individuals are encouraged to grow their garden (see Figure 2). Flowers are awarded for different behaviors that can occur once or be repeatable. For example, participants can earn a blue flower each time they read a skill (repeatable) and one pink sunflower after they read all the skills (single occurrence). Completing home practice and logging into the website are also incentivized, with badges awarded for completing at least one home practice exercise for 4 consecutive days (repeatable) and logging into the website for 7 consecutive days (repeatable).

Following phase 2, we review the study feedback from participants and modify and refine the study design, staff training, enhancements, and intervention content accordingly.

#### Phase 3: A Multifactorial Randomized Controlled Pilot Trial to Test Each Intervention Enhancement for Retention and Adherence

Participants (N=600) are randomized to receive the basic intervention, the intervention plus one or more of the three enhancements, or an emotion-reporting only control condition. Specifically, the study is a multifactorial design in which participants are randomized into one of the following nine arms (approximately 67 per arm): (1) intervention only, (2) intervention + facilitator contact, (3) intervention + ODB, (4) intervention + virtual badges, (5) intervention + facilitator contact + ODB, (6) intervention + facilitator contact + virtual badges, (7) intervention + ODB + virtual badges, (7) intervention + facilitator contact + ODB + virtual badges, and (8) emotion reporting only control.

**Figure 2 figure2:**
[figure not shown]
Example garden plot with virtual flower badges and accompanying key in the virtual badges enhancement.

### Training, Fidelity, and Protection of Human Subjects

All staff members receive training on the overall study design and procedures relevant to their staff assignment, including (1) The technology for participant tracking and data collection (eg, REDCap, Qualtrics, and PingQuest); (2) Procedures for serving as a facilitator in the facilitator contact enhancement (eg, training on scheduling telephone and email correspondence with participants, conducting the brief facilitator telephone calls using a standardized facilitator script (see above) to ensure consistent delivery of facilitator contact); (3) Procedures for serving as a moderator of the ODB; (4) Training on the booster sessions; and (5) Protocol for responding to participant suicidality or distress.

Facilitators are trained on how to handle cases of extreme distress or suicidality expressed over the telephone, via email, or on the ODB. In cases of extreme distress or suicidality, the research staff is trained to emphasize to the participant that MARIGOLD is not therapy and to tell participants to contact 911 in the case of an emergency. As part of the distress-suicidality protocol developed by one of the authors (EA), any signs of distress, however small, is reviewed collaboratively by the facilitator, EA, and the study coordinator (ES) to monitor the safety and well-being of participants and to respond appropriately. Facilitators do not offer medical advice and instead, encourage participants to consult their medical provider, offer resources to find a medical provider if he or she does not have one, and provide relevant resources to participants (eg, a suicide hotline).

Training sessions are conducted initially during the study start-up and when onboarding new staff members, on an ongoing basis as the study protocol is updated across the three phases, and on an as-needed basis to address individual cases and procedural issues. All staff members maintained updated Human Subjects Research training either through Collaborative Institutional Training Initiative or the National Institutes of Health (NIH) Human Subjects Research module.

### Planned Analyses

In all three phases of the study, we plan to conduct intention-to-treat analyses to examine (1) Retention and adherence to the intervention and (2) Preliminary efficacy of the intervention. In phase 3, we will have sufficient power to conduct additional analyses examining (3) Moderators of retention and adherence within each randomization arm, (4) Moderators of the primary and secondary efficacy outcomes within each randomization arm, and (5) Whether intervention effects are mediated by increases in positive emotion.

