## Methods

### Overview of Study Design

In each of the three phases of the MARIGOLD study, individuals with elevated symptoms of depression participate in the same flow of events (see Figure 1). The three study phases differ primarily in terms of the randomization groups and intervention portions of the study sequence (see Figure 1). Specifically, in phase 1, we are tailoring an existing positive emotion skills intervention for individuals with elevated symptoms of depression and are pilot testing the tailored version of the intervention in a randomized controlled trial (RCT) with two control conditions (N=60). In phase 2, we are developing and testing three enhancements aimed at boosting retention and adherence to the Web-based intervention (N=75): facilitator contact, an ODB, and virtual badges. In phase 3, we are conducting a multifactorial, nine-arm pilot trial (N=600) to systematically test these enhancement strategies, individually and in combination. Each component of the study design is described in further detail below.

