#### Retention and Adherence

Retention will be defined as completing the baseline, postintervention, and follow-up assessments. We will categorize retention at each assessment as a binary outcome and will test for differences in the proportions of participants who are retained at each assessment using a binary logistic regression model using dummy variables to represent each arm. Adherence will be assessed in intervention participants only and measured in two ways: (1) the number of skills accessed and (2) the proportion of the intervention completed (ie, the number of pages viewed out of the total possible pages across all lesson modules in the intervention). In the phase 1 pilot, we will report descriptive statistics of adherence in the intervention arm and will explore whether retention differs as a function of arm (intervention vs emotion-reporting control vs waitlist control) using a binary logistic regression, with dummy variables to represent each arm. In the phase 2 pilot, we will explore whether retention and adherence differ as a function of enhancement type using a binary logistic regression for retention and linear regressions for adherence, with dummy variables to represent each arm. In the phase 3 pilot, we will use additional contrast tests to explore whether retention and adherence differ as a function of enhancement type received (no enhancement, facilitator contact, virtual badges, or ODB), as well as whether receiving certain combinations of enhancements offers additional benefits for increasing retention and adherence.

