#### Moderators of Retention and Adherence

In phase 3, we will assess baseline depressive symptom severity, gender, race or ethnicity, and comfort with technology as moderators of retention and adherence. This will allow us to detect whether certain enhancements to the intervention increase adherence or retention for some subpopulations but not others. For each potential moderator, we will rerun the binary logistic regression analyses with a set of interaction variables between the moderator and the dummy condition variables. Due to power limitations, we will not test all four moderators in the same model or explore any interactions among the moderators.

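### Phase 3 is said to have sufficient power for moderator analyses by arm, which about 67 participants per arm do not give, and the only model named for adherence moderators does not match how adherence is defined

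*Protocol article*

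**What the plan says.** All references are to the Protocol article.

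- **Planned Analyses** makes the power statement: "In phase 3, we will have sufficient power to conduct additional analyses examining (3) Moderators of retention and adherence within each randomization arm". The same sentence goes on to item "4) Moderators of the primary and secondary efficacy outcomes within each randomization arm". It gives no alpha, effect size, moderator prevalence or power figure.
- **Phase 3 design section** gives the size: "participants are randomized into one of the following nine arms (approximately 67 per arm"), from a total of 600.
- **Moderators of Retention and Adherence** names four moderators: "we will assess baseline depressive symptom severity, gender, race or ethnicity, and comfort with technology as moderators of retention and adherence". The method is: "we will rerun the binary logistic regression analyses with a set of interaction variables between the moderator and the dummy condition variables". It then adds: "Due to power limitations, we will not test all four moderators in the same model or explore any interactions among the moderators".
- **Retention and Adherence** (under Planned Analyses) treats retention as binary at each assessment. Adherence is assessed in intervention participants only, as a number of skills and as a proportion of pages. For phase 2 the models are given as "using a binary logistic regression for retention and linear regressions for adherence". For phase 3, further contrast tests by enhancement type and by combination are planned.

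**The concern.** The power statement is a positive claim about a property of the design, so it can be checked against the article's own sample size. A moderator-by-arm interaction is a difference between two arm differences, each computed within a subgroup. With a 50:50 moderator, each of the four cells holds about 33 people. Such a test is much less precise than a comparison of two whole arms, and two whole arms of 67 are already small for retention.

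What is at stake is interpretation. The moderator section says the analysis will show whether an enhancement helps some subpopulations and not others, and the Discussion expects to learn which features suit which participants. If power is low, a non-significant interaction carries almost no information, yet a prior claim of adequate power lends it weight.

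The second issue is the model. The moderator section promises results for retention and adherence but describes only a repeat of the binary logistic regressions. Elsewhere those are specified for retention alone, so the article does not say how moderators of adherence will be analysed. Adherence and retention are described as the main focus of the investigation, so the gap is not peripheral.

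**Working it through.** **Inputs from the article.** N = 600 in nine arms. 600/9 = 66.7, which reproduces the stated figure of about 67. Reference retention is about 80%, the rate the phase 1 design section reports for the emotion-reporting control in past research, similar to the intervention. The power statement has no number to reproduce.

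**Assumptions, because the article gives none.** Two-sided alpha 0.05; target power 80%, so the multiplier is 1.96 + 0.84 = 2.80; a binary moderator, 50:50 unless stated; an effect in one stratum and none in the other.

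**Retention, one arm dummy against one reference arm.** Each cell has 66.7 × 0.5 = 33.3.

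Interaction on the logit scale: δ = logit(p₁) − logit(0.80). SE = √Σ 1/(n p(1−p)) over the four cells.

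- 80% to 90%: δ = ln 9 − ln 4 = 0.811. SE = √(3/(33.3×0.16) + 1/(33.3×0.09)) = √(0.5625 + 0.3333) = 0.946. δ/SE = 0.857. Power is about **14%**.
- 80% to 95%: δ = ln 19 − ln 4 = 1.558. SE = √(0.5625 + 1/(33.3×0.0475)) = √(0.5625 + 0.6316) = 1.093. δ/SE = 1.426. Power is about **30%**.

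With a 25:75 moderator the two figures fall to 11% and 21%. On the risk-difference scale, the smallest interaction detectable with 80% power is 35 to 37 percentage points; an improvement confined to one stratum and starting from 80% cannot exceed 20 points.

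Arm size needed for 80% power on the logit scale is 66.7 × (2.80 × SE/δ)²: about 713 per arm for 80% to 90%, and about 258 for 80% to 95%.

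**Continuous outcome (adherence by linear regression, or an efficacy score).** SE = SD × √(2/(n f) + 2/(n(1−f))), with n = 66.7.

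- f = 0.5: SE = √0.12 = 0.346 SD; detectable interaction 2.80 × 0.346 = **0.97 SD**. Power for 0.5 SD is 30%.
- f = 0.25: SE = 0.40 SD; detectable interaction 1.12 SD.

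**More favourable reading: enhancement present v absent, pooled over the eight intervention arms.** Each side has 4 × 66.7 = 267, so every SE halves.

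| Scenario (50:50 moderator) | Arm v arm | Pooled contrast |
|---|---|---|
| Retention 80% to 90% in one stratum, power | 14% | 40% |
| Retention 80% to 95% in one stratum, power | 30% | 81% |
| Continuous outcome, detectable interaction | 0.97 SD | 0.49 SD |

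With a 25:75 moderator, the pooled figures are 30%, 62% and 0.56 SD.

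**Efficacy moderators, all intervention arms v control (533 v 67).** SE = √(2 × (1/266.7 + 1/33.3)) = 0.260 SD; detectable interaction 0.73 SD before any drop-out.

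**Extreme case.** Suppose an effect as large as the contrast between self-guided and supported programmes cited in the Introduction (26% v 72% fully adherent) were present in one stratum and absent in the other. Arm-by-arm interaction power on the logit scale would be 72%, still below 80%.

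**Model for adherence.** Setting the two sections side by side, the logistic regression that could be rerun is the one for retention. Adherence is defined as a count and a proportion, is never dichotomised, and has a linear model in phase 2. The moderator section names no model that fits these definitions.

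**The case against.** The strongest reply is that the arm-by-arm figures take the least favourable reading. The aim of the moderator section is framed in terms of enhancements, and the phase 3 plan for retention and adherence includes contrasts by enhancement type. With balanced arms, a contrast that averages four moderator-by-dummy terms has a quarter of the pairwise variance, so arm dummies do not rule out the pooled comparison. This stands as far as it goes. The moderator section does not restate those contrasts, the power statement speaks of each arm, and 40% for a 10-point effect still does not support the claim.

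Three stronger readings are tempting, and the document does not support them.

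- A reader might infer that the two sections contradict each other on power. They do not. The admitted limitation concerns only fitting four moderators jointly and interactions among them; having power for one moderator at a time but not for all together would be coherent.
- A reader might infer that the adherence moderator model cannot be fitted at all, so that adherence must be cut at an unstated threshold. That goes too far. Pages viewed out of total pages suits a grouped-binomial or fractional logit, and a linear model is already named for phase 2. The likeliest explanation is that the linear regression was omitted from the sentence.
- A reader might infer that sparse cells will routinely make logistic terms inestimable. With a 50:50 moderator and 80% retention, the chance of any cell without drop-out is about 18 × 0.8^33.3, or 1%. It becomes material only for a small subgroup or higher retention, and the article gives neither. Two of the moderators also need not be dichotomised.

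It is also fair that phase 3 is called a pilot, that its comparisons are described as exploring, and that nothing in the article says a null interaction will be read as equal benefit. That limits the harm but does not make the power statement true.

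**Conclusion.** The point holds in two parts. First, the claim of sufficient power for items (3) and (4) is unsupported and, for the stated moderator-by-arm-dummy test, wrong over the plausible range: 14% to 30% power for 10- to 15-point retention effects in one stratum, and a detectable interaction near 1 SD for a continuous outcome. Pooling over enhancements brings this to 40% to 81% and about 0.5 SD, so only large interactions with a balanced moderator would be covered. Second, the named moderator model does not match adherence as defined; this is a specification gap that is easily closed.

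The figures rest on assumed alpha, moderator prevalence and effect sizes, and on the single retention rate of about 80% in the article. Drop-out makes the efficacy figures worse: at 80% retained, 0.97 SD becomes 1.08 SD. The mediation analysis, item (5), pools intervention arms and is not covered by this point. These are secondary analyses, and the primary efficacy comparison is not affected. The text should be corrected, but the trial's main conclusions do not depend on it.

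**What to change.** - **Planned Analyses:** remove the sufficient-power wording for items (3) and (4). Describe the moderator analyses as exploratory, reported as interaction estimates with confidence intervals, and state that a null interaction will not be read as equal benefit.
- **Moderators of Retention and Adherence:** test moderators of enhancement effects through the enhancement-level contrasts planned for phase 3, defined as each enhancement present v absent across the eight intervention arms. Keep the control-arm comparison for retention, and the combination contrasts, as secondary.
- **Model by outcome:** use the linear model already named for adherence, with robust standard errors, or a fractional logit; keep logistic regression for retention.

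**Cost.** The power statement becomes less favourable. The change is slightly more than wording, because the moderator test and the adherence model are re-specified, and pooled contrasts average over the other enhancements. No change to design or data is needed. Since the article reports data collection complete and analysis under way, the re-specification should be dated and reported as such.

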#### Retention and Adherence

Retention will be defined as completing the baseline, postintervention, and follow-up assessments. We will categorize retention at each assessment as a binary outcome and will test for differences in the proportions of participants who are retained at each assessment using a binary logistic regression model using dummy variables to represent each arm. Adherence will be assessed in intervention participants only and measured in two ways: (1) the number of skills accessed and (2) the proportion of the intervention completed (ie, the number of pages viewed out of the total possible pages across all lesson modules in the intervention). In the phase 1 pilot, we will report descriptive statistics of adherence in the intervention arm and will explore whether retention differs as a function of arm (intervention vs emotion-reporting control vs waitlist control) using a binary logistic regression, with dummy variables to represent each arm. In the phase 2 pilot, we will explore whether retention and adherence differ as a function of enhancement type using a binary logistic regression for retention and linear regressions for adherence, with dummy variables to represent each arm. In the phase 3 pilot, we will use additional contrast tests to explore whether retention and adherence differ as a function of enhancement type received (no enhancement, facilitator contact, virtual badges, or ODB), as well as whether receiving certain combinations of enhancements offers additional benefits for increasing retention and adherence.

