#### Run-In Period

Upon consenting to participate in the study, all participants begin the 7-day run-in period to screen participants for compliance. This run-in period must be completed to qualify for randomization. Each day during the 7-day run-in period, participants receive an email with a link to a brief Web-based survey, where they complete a daily emotion report using the revised Differential Emotions Scale (DES; see Multimedia Appendix 1) [35]. Participants who complete at least four emotion reports within the first 7 days are randomized to the study. Participants who do not complete at least four emotion reports within the first week are given a second opportunity to do so. If they do not complete at least four emotion reports within the second 7-day run-in period, they are not randomized in the study. We have used this run-in period in our prior research to screen out noncompliant participants [53].

In addition to the daily emotion reports, participants also complete ecological momentary assessments (EMAs) of their positive and negative emotion [56] during the run-in period. Specifically, participants receive SMS text messages (short message service, SMS) on their mobile devices three times per day for 3 days over the course of the week, prompting them to answer questions regarding their current emotional experience. In phases 2 and 3, participants are also completing measures of their daily negative stressors (assessed using the Daily Inventory of Stressful Events, DISE) [57,58] during the run-in period. The DISE is included in the brief Web-based survey sent to participants (see Multimedia Appendix 1). Although we are collecting EMAs and DISE during the run-in period, we are not using this data to inform whether participants are randomized to the study.

Eligibility criteria for participation.Eligibility criteriaBe 18 years or olderHave daily access to the internetOwn a mobile phoneLive in the United StatesBe fluent in the English language (reading and writing)Have elevated depressive symptoms (8-item Patient Health Questionnaire, PHQ-8, depression score ≥5) [55]

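### The phase 3 retention and adherence comparisons name no baseline covariate, although stratification factors and run-in response data are available; adjusting for them could give a modest gain in precision

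*Protocol article*

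**What the plan says.** Under Planned Analyses, Retention and Adherence, retention at each assessment is tested "using a binary logistic regression model using dummy variables to represent each arm". For phase 2 the models are described as "using a binary logistic regression for retention and linear regressions for adherence, with dummy variables to represent each arm". For phase 3 the article says "we will use additional contrast tests to explore whether retention and adherence differ as a function of enhancement type received", and it also plans to look at combinations of enhancements. No covariate is named in that section.

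Covariates do appear in two neighbouring sections:

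- Preliminary Efficacy has a covariate-selection sentence, placed with the growth-curve models for the efficacy outcomes.
- Moderators of Retention and Adherence brings baseline depressive severity, gender, race or ethnicity and comfort with technology into the phase 3 models, but as interactions with arm and one moderator at a time.

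The Randomization section states that phases 2 and 3 are stratified by gender and PHQ-8 level (three levels in phase 2, four in phase 3).

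The Run-In Period section describes what is recorded before allocation. "Participants who complete at least four emotion reports within the first 7 days are randomized to the study"; those who fall short "are given a second opportunity to do so". Text-message prompts about current emotion are sent "three times per day for 3 days over the course of the week", and these are stated not to affect entry.

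**The concern.** Preliminary Efficacy says that the investigation is mainly about optimising adherence and retention, so the phase 3 enhancement contrasts carry its main question. The models for them, as described, contain arm and nothing else.

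Two kinds of baseline information are left out. The first is the stratification factors. If a stratification factor is prognostic, leaving it out of a linear model makes the usual standard errors too large, because the balance obtained by design is not credited in the analysis. The second is the graded run-in data. The article uses the run-in to screen out non-compliant people, so it already treats response there as informative about later compliance. The daily reports then serve only as a pass or fail gate, and the prompt responses have no role in these models.

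At stake is some precision in contrasts of about 67 against 67 (single arms) or about 267 against 267 (one enhancement present or absent). Validity is not at stake.

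**Working it through.** **Inputs from the article.** Phase 3 has 600 participants in nine arms: 600/9 = 66.7, which agrees with the stated figure of about 67 per arm. The eight intervention arms hold 8 × 66.7 = 533, so each enhancement main effect compares about 267 with 267. Phase 2 has 75 participants, 25 per arm. Randomised participants have 4 to 7 daily reports out of 7. The prompts number 3 × 3 = 9 in a run-in week. Retention in earlier research was about 80%.

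**Assumed, because the article gives no figure.** Two-sided alpha of 0.05; 80% unadjusted power as the reference; and the share of outcome variance explained by the covariates (R²). There is no stated power calculation to reproduce.

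**Step 1: how much R² survives the entry rule.** A latent engagement trait was simulated with a binomial report count over 7 days, entry at four or more, one second attempt, and 9 prompts. Three settings were used, with 75% to 89% passing the run-in.

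| Latent correlation with outcome | R², report count, no entry rule | R², report count, after entry rule | R², adding prompts and second-attempt flag |
|---|---|---|---|
| 0.3 | 0.048–0.066 | 0.025–0.028 | 0.037–0.044 |
| 0.5 | 0.134–0.183 | 0.073–0.082 | 0.108–0.128 |
| 0.7 | 0.264–0.359 | 0.153–0.178 | 0.239–0.266 |

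The entry rule removes about 40% to 60% of the report count's R². Low to moderate association leaves a combined R² of about 0.04 to 0.13.

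**Step 2: adherence (linear model).** Power = Φ(2.80/√(1 − R²) − 1.96).

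- R² = 0: 80.0%
- R² = 0.04: 2.80/√0.96 = 2.86, minus 1.96 = 0.90, giving 81.6%
- R² = 0.10: 84.0%
- R² = 0.13: 2.80/√0.87 = 3.00, minus 1.96 = 1.04, giving 85.2%
- R² = 0.24 to 0.27: 89.5% to 90.6%

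So the gain is roughly 2 to 5 points over the range 0.04 to 0.13, and about 10 if the association is strong. At R² = 0.10 the difference detectable with 80% power falls from 0.484 to 0.459 SD (67 against 67) and from 0.242 to 0.230 SD (267 against 267). In sample-size terms, 533/(1 − R²) − 533 is 22 extra participants at R² = 0.04 and 80 at 0.13.

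**Step 3: retention (logistic model).** 4,000 simulated trials per setting, marginal rates held fixed, Wald test with and without one standardised covariate.

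| Log odds ratio per SD | 267 v 267, 70% v 80%: unadjusted → adjusted | 67 v 67, 60% v 80%: unadjusted → adjusted |
|---|---|---|
| 0 | 76.0% → 76.1% | 73.6% → 73.0% |
| 0.3 | 76.3% → 76.6% | 72.6% → 73.1% |
| 0.6 | 76.0% → 78.9% | 72.4% → 74.9% |
| 1.0 | 75.3% → 82.0% | 72.4% → 79.2% |

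The range is 0 to 7 points. On the latent logistic scale, R² = g²/(g² + π²/3), where g is the log odds ratio per SD: 0.03, 0.10 and 0.23 for g = 0.3, 0.6 and 1.0. The 7-point end therefore needs a stronger covariate than the 0.04 to 0.13 of step 1; within that range, gains of about 1 to 3 points are more likely.

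**Step 4: phase 2.** At 25 against 25, power for 70% against 80% retention is about 13%; sample size is the limit there. With about 80% retained, 0.20 × 75 = 15 are not retained. The full set would add six terms (two for PHQ-8 level, one for gender taken as two categories, three from the run-in) to two arm terms: eight terms on about 15 events, which risks overfitting or separation.

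**The case against.** The strongest objection is that the phrase about dummy variables says how arm is coded and does not exclude covariates. Preliminary Efficacy uses the same phrase and then refers to covariates. A condensed article may also leave the covariate list to an analysis plan that is not shown. This stands in part: the article does not say that arm is the only term. But it does discuss baseline variables for these outcomes, as one-at-a-time moderators, and it places its covariate-selection sentence with the efficacy models. Adjusting the main comparisons is thus a definite improvement on the model as described, and more than a complaint about a missing list.

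It is also fair that the unadjusted comparison is valid, that the comparisons are called exploratory, and that no power target is set for any enhancement contrast. All of that stands.

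A reader might infer that the run-in is a baseline measurement of the outcomes themselves, and that the contrasts therefore lose substantial power, with 90% to 94% within reach instead of 80%. The documents do not support this. The run-in records answers to emailed surveys and text messages. Retention is completion of paid assessments, and adherence is skills accessed and pages viewed over a 7-week course. No correlation between them is given. Power of 90% to 94% needs a correlation of 0.5 to 0.6 among people who have already passed the entry rule (R² of 0.25 to 0.36); the simulation reached only 0.24 to 0.27, and only with a latent correlation of 0.7.

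**Conclusion.** The point holds as an efficiency recommendation for phase 3. The comparisons as described name no baseline covariate, while the stratification factors and pre-randomisation response data are available. The analysis is valid but may be less precise than the data allow.

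The size is modest and rests on an assumed association: about 2 to 5 power points for adherence from an 80% reference, and 0 to 7 for retention with the upper end requiring a strong covariate. If run-in response is not prognostic among those who passed, it brings no gain. Any benefit from the stratification factors depends in the same way on their being prognostic, and is not included in these figures. For phase 2, adjustment cannot make up for 25 per arm.

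**What to change.** In the phase 3 retention and adherence models, include gender, PHQ-8 level as stratified, the run-in daily-report count, a flag for a second run-in attempt, and the number of text-message prompts answered. Define the report and prompt counts for the qualifying run-in week, since the article does not say whether prompts are repeated in a second attempt. Report retention as standardised risk differences from the adjusted logistic model. State the expected gain as an assumption.

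In phase 2, add at most one or two terms, such as the report count, and treat the result as exploratory.

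The cost is a few model terms and no new data. The adjusted odds ratio is conditional on the covariates; the standardised risk difference restores a marginal effect. The Results section says that data collection is complete and analysis is under way, so the covariates should be fixed before arm-level results are seen. If that is no longer possible, the adjusted analysis should be labelled as added later and shown beside the unadjusted one.
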